### 3. AIMS

The present study describes the second phase of the *ConCure-SM* project. The objectives of this pilot and feasibility study are as follows:

1. To determine how many people accept the invitation to participate in the study.
2. To determine how many participants receive the intervention.
3. To estimate recruitment and refusal rates, and 6-month follow-up rates.
4. To estimate ACP completion during the 6-month follow-up (primary study outcome).
5. To estimate occurrence of serious adverse events (SAEs) and adverse events (AEs) during the 6-month follow-up.
6. To assess, qualitatively, the acceptability of the recruitment processes, assessments, intervention delivery and secondary outcome measures with key stakeholders.
7. To measure changes in secondary outcome measures.
8. To explore the barriers and facilitators to implementing ACP in pwPMS, and the influence of the clinical setting.
9. To inform the sample size estimation for a subsequent RCT, should this be feasible.

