## 5.3 Outcome Measures

A range of measures will be collected to capture the full process of ACP and whether the *ConCure-SM* intervention has any effect on completion of an advance care plan document (primary outcome measure), congruence in treatment preferences between pwPMS and their carers, quality of patient-clinician communication, and caregiver burden. In addition, since a study-related increase in emotional burden can't be excluded, serious adverse events (SAE: admission to psychiatric ward, suicide attempt, death) will be monitored by the independent Data and Safety Monitoring Committee (DSMC). Mood symptoms will be assessed at baseline and during follow-up.

We are aware that long-term outcomes (chiefly the concordance between preferred and received EOL care and treatments) are warranted. However, the MS trajectory further challenges the collection of this outcome in the typical timeframe of a clinical trial. The assessment of this outcome in pwPMS could be feasible by focusing on the late stages of the disease only. In line with the principles of ACP, we agreed not to narrow the inclusion criteria deserving this relevant outcome to future studies.

We will use the published Italian version of the following inventories: CPS [Giordano 2008], HADS [Costantini 1999], OPTION [Goss 2007], MSQOL-29 [Rosato 2016], ZBI [Chattat 2010].

The 4-item ACP-E and the QOC inventories will be translated and culturally adapted from source language (section 5.3.8).

**Table 2.** Secondary outcome measures of the trial (in alphabetical order)

| Scale name   | Assessor | Construct          | Author       | Italian version | Timing   |
|--------------|----------|--------------------|--------------|-----------------|----------|
| 4-item ACP-E | Patient  | ACP engagement     | Sudore 2017  | –               | T0/T1/T2 |
| eCPS         | Patient  | Role preferences   | Degner 1997  | Solari 2013     | T0       |
| HADS         | Patient  | Mood symptoms      | Zigmond 1983 | Costantini 1999 | T0/T1/T2 |
| MSQOL-29     | Patient  | Health-related QOL | Rosato 2016  | Rosato 2016     | T0/T2    |

| OPTION  | Third observer | SDM (physician's skills)                   | Elwyn 2005     | Goss 2007    | –        |
|---------|----------------|--------------------------------------------|----------------|--------------|----------|
| QOC     | Patient        | Communication quality (physician's skills) | Engelberg 2006 | –            | T1       |

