### **5.3.7 Mood symptoms**

*HADS* - The Hospital Anxiety and Depression Scale (HADS) is a self-assessed questionnaire consisting of 14 multiple-choice (0–3 Likert scale) items probing symptoms of anxiety (7 items) and depression (7 items). HADS anxiety (HADS-A) and depression (HADS-D) scores range from 0 (no symptoms) to 21 (most severe symptoms) [Zigmond 1983]. We choose HADS because it is a screening tool with robust psychometric properties, and has been validated in several languages, including Italian [Costantini 1999]. Furthermore, by omitting items assessing somatic symptoms, and thereby limiting false positive findings, the scale is suitable for use in persons with medical conditions [Herrmann 1997]. A cutoff score of 8 or above was recommended for MS patients, since it was found to be an accurate indicator of major depression (90% sensitivity, 87% specificity) and generalized anxiety disorder (88.5% sensitivity; 81% specificity) in this population [Honarmand 2009]. We will use the Italian version of the HADS [Costantini 1999].

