### **5.3.8 Safety data monitoring plan**

A thorough safety data monitoring plan will be developed and implemented in order to monitor participant safety, as well as data integrity. Adverse events (AEs) will be recorded by the site and reported to the PI immediately.

For the *ConCure-SM* Phase 2 study, a Serious Adverse Event (SAE) will be defined as an emotional breakdown resulting in hospitalization, suicidal attempt, or death. AEs will include the following: a) any contact to the patient referring physician due to the occurrence of emotional problems during the study; b) an increase of  $\geq 20\%$  in the HADS Anxiety or/and depression score [Puhan 2008]. AEs will be monitored to ensure that the AE was caused by the study intervention, and not some coincidental issue. AEs will be collected and reported to the study PI as well as the DMSC.

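### The adverse-event rule of a 20% or greater HADS rise demands a different point change at each baseline and would flag roughly 30–70% of patients with no true change

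*Protocol*

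**What the plan says.** Section 5.3.8 gives two routes to an adverse event. Route (a) is "any contact to the patient referring physician due to the occurrence of emotional problems during the study". Route (b) is a rise of 20% or more "in the HADS Anxiety or/and depression score". Route (b) carries no minimum point change, severity floor or rule for a baseline of 0, and it does not name the score from which the rise is measured; T0 is the natural reading. The section then adds an attribution step: "AEs will be monitored to ensure that the AE was caused by the study intervention, and not some coincidental issue". Serious events (hospitalization for emotional breakdown, suicide attempt, death) are defined separately.

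Section 5.3.7 describes "items probing symptoms of anxiety (7 items) and depression (7 items", each item scored 0–3, and says that the subscale "scores range from 0 (no symptoms) to 21 (most severe symptoms". It also endorses a cut-off of 8 or above for people with MS, which section 5.3.8 does not use. Tables 1 and 2 place the HADS at T0, T1 and T2.

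Section 3 makes the event rate an objective: "To estimate occurrence of serious adverse events (SAEs) and adverse events (AEs) during the 6-month follow-up". Section 5.2.1 states that the study is non-randomized and that every participant receives the intervention.

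**The concern.** A percentage change on a short whole-number scale that starts at 0 is a different test for each patient. Where symptoms are few, one step on one item is enough. Where they are many, several points are needed, and near the top no rise can qualify. Each patient is also tested four times (two subscales, two visits), and any one pass counts.

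The study's stated worry is added emotional burden, and this is its only score-based AE trigger. If most flags are retest noise in people with low scores, the AE rate says little about the intervention. It would also be a poor planning figure for the later randomized trial, since there is no control group from which to learn the background rate.

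**Working it through.** **Step 1: points needed (exact, no assumptions).** For an integer baseline b > 0, the smallest qualifying rise is 0.2 × b rounded up, and b plus that rise must not exceed 21.

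| Baseline | 0.2 × b | Points needed | Reachable? |
|---|---|---|---|
| 0 | – | undefined (division by 0) | – |
| 1–5 | 0.2–1.0 | 1 | yes |
| 6–10 | 1.2–2.0 | 2 | yes |
| 11–15 | 2.2–3.0 | 3 | yes |
| 16–17 | 3.2–3.4 | 4 | yes (17 + 4 = 21) |
| 18–21 | 3.6–4.2 | 4–5 | no (1.2 × 18 = 21.6 > 21) |

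The ordering that follows is odd:
- 1 to 2 is an AE (1.2 × 1 = 1.2).
- 7 to 8 is not (1.2 × 7 = 8.4), although it crosses the cut-off in section 5.3.7.
- 15 to 17 is not (1.2 × 15 = 18).
- 18 to 21 is not.

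**Step 2: a hand check of the noise.** The protocol gives no HADS mean, SD or retest reliability, so these are assumptions. Take SD 4 and reliability 0.85. The error SD is 4 × √(1 − 0.85) = 1.55, and the SD of the difference between two readings of a stable patient is 1.55 × √2 = 2.19. With a half-point continuity correction, and ignoring regression to the mean:
- a rise of 1 or more has probability P(Z ≥ 0.5/2.19) ≈ 0.41;
- a rise of 2 or more has probability P(Z ≥ 1.5/2.19) ≈ 0.25.

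That is for one subscale at one visit.

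**Step 3: simulation with no true change.** There were 200,000 patients per scenario. Scores were rounded and truncated to 0–21, and T1 and T2 were each compared with T0. Assumptions: mean 5, 7 or 9; SD 3.5 or 4.5; true-score correlation between subscales 0.6; error correlation 0.3. A patient is flagged if either subscale qualifies at either visit.

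| Reliability | Any rise from 0 counted | Baseline-0 subscales excluded |
|---|---|---|
| 0.80 | 55–68% | 55–61% |
| 0.85 | 51–65% | 50–59% |
| 0.90 | 44–61% | 43–54% |
| 0.95 | 31–52% | 30–46% |

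Overall this is roughly 30–70%, or 0.30 × 40 = 12 to 0.70 × 40 = 28 of 40 patients. Varying the error correlation from 0 to 0.8 (mean 7, SD 4, reliability 0.80) moves the rate from 69% down to 56%. For one subscale at one visit the rate is lower, 22–36% at reliability 0.70–0.85.

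**Step 4: size of the ceiling gap.** With SD 4 and mean 5–9, about 0.2–3% of patients have a subscale at 18 or above. At mean 7 it is about 0.8%, or 0.008 × 40 = 0.3 patients; about 0.04% are that high on both subscales.

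**Step 5: what a fixed threshold trades.** As an illustration only, take a 4-point rule with mean 7, SD 4 and reliability 0.80, 0.85, 0.90 and 0.95. It flags 25%, 18%, 9% and 1% of stable patients. If both subscales truly worsen by 2 points, it flags about 64%, 59%, 52% and 35%, against 92–93% for the 20% rule.

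**The case against.** Several counter-arguments have force.

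- **The ceiling.** A reader might infer that a patient scoring 18 or above can never be flagged. The text does not support this. The rule applies to either subscale, so such a patient can qualify on the other one; route (a) and the serious-event definition apply at any score. Only a patient at 18 or above on both subscales is beyond the HADS trigger, and step 4 shows how rare that is. A fixed rise of 4 points has the same unreachable range (18 + 4 = 22), so the ceiling alone is no argument for a fixed threshold of that size.
- **The false-flag rate.** A reader might state flatly that half or more of stable patients are flagged. That depends on assumed inputs. It holds in these scenarios up to reliability of about 0.85, is around half at 0.90, and mostly fails at 0.95.
- **Sensitivity.** A stricter rule always gives fewer false flags. Step 5 shows that it also misses more true worsening.
- **Consequences.** None of the phase III progression criteria in section 6 uses the AE rate, and no stopping rule is stated. HADS change is analysed anyway under section 5.5.2. A sensitive trigger errs towards caution.
- **Source.** The 20% figure carries a citation. By its title, that is a minimal-important-difference study of the HADS in chronic obstructive pulmonary disease. It cannot be judged here, but no source alters the arithmetic in step 1.

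These points limit the severity and do not remove the defect. The attribution step does not rescue the rate either: with no comparison group, a review cannot tell whether a one-point rise is noise or effect, and it cannot recover rises that the rule never flagged.

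**Conclusion.** The point holds at moderate severity. It is certain from the protocol's own scale that the rule needs 1 to 4 points depending on baseline, is undefined at 0, is unreachable for a subscale at 18–21, and passes over a move from 7 to 8. The false-flag share of roughly 30–70% is conditional: it is per patient, over both subscales and both visits, and rests on the assumed mean, SD and reliability. Even at the low end, about 12 of 40 stable patients would count as having an AE, with no background rate to set this against. The AE estimate for Objective 5 would therefore be hard to interpret.

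A reader might go further and treat this as a flaw that must be cured before the study can run. The protocol does not support that: no stated decision turns on the AE rate, and the underlying HADS scores are collected and analysed in any case.

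**What to change.** In section 5.3.8, name T0 as the reference score and replace the percentage with one fixed absolute point increase, the same for every patient and each subscale. The Trial Steering Committee and the safety committee should set it before any data are seen; no particular value is prescribed here. Beside it, report the number of patients who move from below 8 to 8 or above on each subscale, and list individually those whose baseline is too near 21 for the chosen rule to fire.

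The cost is a few lines of text and a flag on the trial platform; no new data are needed. The drawback is that fewer small rises would count as AEs, and sensitivity to modest true worsening falls as the threshold rises. Those changes stay visible in the HADS change analysis. The count of moves across 8 is itself a one-point trigger for a patient at 7, so it should stand beside the fixed-point rule as a description and not be read as a noise-free measure.

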### **5.3.9 Linguistic validation**

The 4-item ACP-E and the QOC inventories will be translated and culturally adapted from source language to Italian following accepted guidelines [Guillemin 1993; Wild 2009]. The main steps in this process are the following:

*Forward translation* - The aim of this step is to produce a version semantically and conceptually as close as possible to the original. Two qualified translators, both living in the target country, will produce two independent translations. A panel consisting of the translators and HPs will review the forward translations and a consensus version will be produced.

*Backward translation* - The consensus translation generated in step 1 will be independently translated back into the source language by a third qualified translator, living in the target country. The backward translation will be produced without access to the original version and without consulting the other translators.

*Consensus meeting* - At a meeting between those participating in step 1 and the backward translator, the backward translation will be compared with the original, and further refinements to the target version will be made. Differences will be resolved by discussion. After translation into the target language, the instrument will be administered to and tested (debriefed) involving 5 to 10 users. Results of cross-cultural testing will be discussed in a joint meeting.

## **5.4 Nested qualitative study**

Our referral framework was the mixed methods approach which, by integrating the quantitative findings with the qualitative findings, aims to provide a more comprehensive picture of the intervention than either method can do [Craig 2008]. Quantitative and qualitative data will be collected in parallel and then analyzed and integrated using Normalization Process Theory (NPT). We will perform semi-structured one-on-one interviews with pwPMS and SOs chosen using a maximum variation strategy, and FGMs of physicians involved in intervention delivery and other HPs from the center (Figure). For the pwPMS and the SOs the personal semi-structured interviews were considered most appropriate to limit interview burden and hopefully make it easier for participants to express their feelings, and recount their experiences of the intervention. For the patient referring physicians and the other HPs we chose the FGMs as they promote interaction and exchange of ideas. A minimum of 10 interviews (five with pwPMS and five with SOs) and two FGMs will be held, the final number depending on the achievement of 'data saturation' [Denzin 2000]. We will use NPT to determine if, and in what ways, the *ConCure-SM* intervention can be successfully 'normalized' (embedded) into clinical practice. Further, we will use qualitative data to identify required modifications and to develop practical strategies for enabling and sustaining the *ConCure-SM* intervention delivery in clinical settings.

### **5.4.1 Personal semi-structured interviews**

The interviews will take place within two months of trial completion, and last no more than an hour. We plan to conduct a minimum of five pwPMS and five SOs interviews. Data will be analyzed after a set of two to three interviews and used to decide the characteristics of the next interviewee, revise the interview guide (if necessary), and indicate when recruitment should stop because of adequate evidence of 'data saturation' (a point where data collected from the conducting additional interviews became redundant, adding no more to the understanding of the study phenomenon) [Denzin 2000].

The 'maximum-variation' selection strategy will be designed to include participants with varying characteristics and levels of outcomes. To reduce social desirability response bias, the interviews will be conducted by researchers not involved in the [ConCure-SM](#) intervention delivery. The interview will be audio recorded, transcribed, and analyzed using thematic analysis, guided [Braun 2006]. Participant consent for the interviews will be sought separately. The interviews will provide important feedback on participant perception of the quality of the intervention provided, and will serve as a process measure. Insights from this qualitative analysis will serve to inform fine-grain intervention refinement.

Before starting, interviewees will be informed of study aims and requirements, and provide written consent. The interviewer will then explain that the aim of the interview was to obtain participant feedback on experience of the pilot study and stress that positive and negative experiences of, and feelings about, the intervention are welcome. Participants will be assured that the interviews are confidential, and that the audio recordings and subsequent transcripts will be fully anonymized. The interviewer will then pose each question in turn, neutrally (so as to not suggest any particular reply) and in an open-ended fashion (to allow many possible replies). As each question is discussed, follow-up questions will clarify and explore participant responses. Participants will be also encouraged to elaborate on any pertinent themes or views that emerge. The interviewer will note any potentially informative non-verbal gestures. At the end of the interview, the interviewer will verbally summarize the key points and ask the participant if the summary is full and correct.

#### **5.4.2 Focus group meetings (FGMs)**

Two FGMs, each with 6-10 physicians who delivered the intervention and HPs from the participating centers will be conducted. Each meeting will last about 2 hours, and will be conducted by two psychologists specifically trained in qualitative research. The aim is to collect insights and living

experiences about the intervention and to identify possible barriers to its implementation; they will provide important feedback on the intervention and on factors that can enable its implementation and adoption. For this reason, HPs other than the physicians involved in the ACP conversation will be involved.

All participants will provide written informed consent prior to participating. The meetings (teleconferences) will be audio-recorded and transcribed verbatim. They will be conducted by a single facilitator, whose job is to engage all participants, promote exchange, moderate conflicts, ensure that all pre-specified topics will be adequately covered, and allow exploration of any pertinent issues that arise. He/she will first explain the purpose of the meeting and ask participants to introduce themselves. He/she will then introduce each topic in turn, in an open-ended fashion. At any point the facilitator can probe for further information and ask follow-up questions to stimulate further discussion. After all pre-specified topics are fully discussed, the facilitator will summarize the main points, and ask for further feedback and whether all concerns have been fully aired. The co-moderator will take notes and oversee the audio recording. Subsequently, the facilitator will produce a report from the audio recordings/transcript and his/her field notes, which will be submitted to participants for review (respondent validation).

## 5.5 Data analysis

### 5.5.1 Study power

As this is a pilot and feasibility study, a formal sample size calculation is not required. We aim to recruit at least 40 pwPMS from six centers to assess feasibility across a diverse range of participants including those with different care needs and living conditions. There are no data available on the occurrence of ACP in pwPMS: by hypothesizing a proportion in the pwPMS population of 10%, a sample size of 35 subjects achieves a power of 90%, assuming a type I error of 5%, to detect a proportion of ACP documentation of 30% (Table 2). By hypothesizing a proportion in the pwPMS population of 8%, a sample size of 35 subjects achieves a power of 95%, assuming a type I error of 5%, to detect a proportion of ACP documentation of 30% (Table). By adding 15% of drop outs or incomplete data, 40 pwPMS should be recruited.

**Table 3.** Estimated sample size for one-sample comparison of proportion to hypothesized value.  $H_0$  is the value in the population,  $H_i$  is the alternative value.

| $H_0$ | $H_i$ | Alpha (two-sided) | Power | Estimated required sample size (n) |
|-------|-------|-------------------|-------|------------------------------------|
|-------|-------|-------------------|-------|------------------------------------|

|      |      |      |      |    |
|------|------|------|------|----|
| 0.10 | 0.30 | 0.05 | 0.90 | 35 |
| 0.08 | 0.30 | 0.05 | 0.95 | 35 |

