To optimize the alignment between patient goals and the care they receive, HPs should integrate best practices in ACP in the care of pwPMS. As from a recent guideline on palliative care in MS there is no evidence of the effects of ACP for pwPMS [Solari 2020]. However, there is some evidence from non-neurological progressive and life-threatening illnesses that ACP decreases the use of life-sustaining treatment, increases hospice/palliative care, reduces hospitalizations and increases compliance with patients’ end of life wishes [Brinkman-Stoppelenburg 2014]. Further, there is evidence that MS patients and caregivers often would like to discuss the issues of death and dying and HPs should acknowledge and encourage these discussions [Golla 2015, Golla 2016]. Often HPs leave EOL discussions until the later stages of progression in MS [Walter 2019]. Patients react in different ways on discussion of future planning: a small study showed that some MS patients made clear decisions, some undertook some planning but without a clear AD and some were still “hoping for a cure” and did not wish to look ahead [Chen 2013]. However, caregivers may be left having to take difficult decisions if no planning has taken place and this was stressful for them [McCurry 2013].

*ConCure-SM* is a project aimed to set up and evaluate the efficacy of an ACP intervention for pwPMS in Italy. The study focuses on HP training, and originates from a multidisciplinary panel of professionals from the *Gruppo di Studio di Bioetica e Cure Palliative* of the *Società Italiana di Neurologia*.

The SDM model described above is the theoretical framework of the project [Archer 2018, Coulter 2020, Elwyn 2012]. The Medical Research Council (MRC) framework for developing and evaluating complex interventions is the methodological framework of the project. The MRC framework has a phased approach, from a pre-clinical research phase to a final phase in which the intervention is introduced into the health service, leading to a theory-driven intervention: a "bottom up" development which guarantees to enter a phase III trial with an appropriate theory and pilot work [Craig 2008]. Further, both quantitative and qualitative methods are used and integrated within the framework, in order to better appraise the effects of the (complex) intervention both as a whole and on its components.

Our study hypotheses are that *ConCure-SM* intervention will produce:

- Higher completion of an ACP document.

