### 5.2.2 Participant eligibility

We chose to focus our study population on pwPMS, as evidence suggests that patients may be less likely to engage in ACP if they perceive themselves as 'too healthy' [Schickedanz 2009].

PwPMS (in- or outpatients) will be included if they:

- Are ≥18 years of age;
- Were diagnosed with primary or secondary PMS [Lublin 1996] from one or more years before inclusion;
- Are able to communicate in Italian;
- Gave written consent;
- Have one or more of the following conditions that would make ACP relevant:
  - Express desire for ACP;
  - Raise questions about their future;
  - Talk about hastening death or medically assisted suicide;
  - High risk for death within two years using the 'Surprise Question' [Downar 2017];
  - High risk for development of severe cognitive compromise/dementia within two years;
  - High risk for development of impairments preventing communication within two years;
  - Significant suffering (e.g. uncontrolled physical symptoms, psychosocial or existential issues).

PwPMS will be excluded if they have one or more of the following:

- Severe cognitive compromise (MMSE < 19) or impairments preventing communication;
- Psychosis or other serious psychiatric conditions;
- Advance care plan document completed.

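### The 8–10% used to size the study is a guess for all pwPMS, not the untreated six-month rate of the patients enrolled, so exceeding it would not show that the intervention raises ACP completion

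*Protocol*

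**What the plan says.** Section 5.5.1 says that a pilot needs no formal sample size calculation and then gives one. It concedes that "There are no data available on the occurrence of ACP in pwPMS" and proceeds "by hypothesizing a proportion in the pwPMS population of 10" per cent, "assuming a type I error of 5" per cent, with 35 subjects giving 90% power "to detect a proportion of ACP documentation of 30" per cent. A second scenario follows: "By hypothesizing a proportion in the pwPMS population of 8%, a sample size of 35 subjects achieves a power of 95" per cent. Table 3 labels this a one-sample comparison with two-sided alpha and defines H0 as the value in the population.

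Section 5.5.2 defines the primary endpoint as the proportion of pwPMS who complete an ACP in the six-month period. It names no test for that endpoint, but sets a general significance threshold of p < 0.05.

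Section 5.2.2 lists among the exclusions "Advance care plan document completed". It also requires at least one of seven conditions that make ACP relevant, the first being "Express desire for ACP". Section 5.2.1 says that all participants receive the intervention. The first hypothesis in section 2 is that the intervention will produce "Higher completion of an ACP document".

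**The concern.** The reference value and the endpoint describe different things.

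- **Population.** H0 refers to pwPMS in general. The study enrols those with a reason to consider ACP, and wanting it is reason enough.
- **Starting point.** A population proportion counts people who already have a plan. Participants all start at zero.
- **Time frame.** A population proportion accumulates over any past period. The endpoint counts completions within six months.

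There is no control group, and the protocol gives no untreated rate for eligible patients. The word *higher* in the first hypothesis needs a comparator, and the only number on offer is the assumed 8–10%. A result significantly above 10% could then be reported as support for that hypothesis, although the comparison says nothing about what these patients would have done without the intervention.

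**Working it through.** **1. The plan's own figure.** Inputs from section 5.5.1 and Table 3: p0 = 0.10 or 0.08, p1 = 0.30, two-sided alpha 0.05, power 90% or 95%. One-sample normal approximation:

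n = [(z(1−α/2)·√(p0(1−p0)) + z(power)·√(p1(1−p1))) / (p1−p0)]²

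- p0 = 0.10, 90% power: [(1.960×0.300 + 1.282×0.458)/0.20]² = (1.175/0.20)² = 34.5, so 35. Power at 35 is 90.3%.
- p0 = 0.08, 95% power: [(1.960×0.271 + 1.645×0.458)/0.22]² = (1.285/0.22)² = 34.1, so 35. Power at 35 is 95.4%.

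Both figures reproduce. The arithmetic is sound; the question is what p0 stands for.

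**2. The rejection rule.** For the exact binomial test at n = 35 against 10%, the upper-tail probability P(X ≥ 8 | 0.10) is 0.020, so the test rejects at 8 or more completers (22.9%). At n = 40 it rejects at 9 or more, with upper-tail probability 0.015.

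**3. Rejection when the intervention has no effect.** Let q be the untreated six-month completion rate in eligible patients. The documents do not give q, so the values below are assumptions. The rejection probability is P(X ≥ 8 | 35, q) or P(X ≥ 9 | 40, q).

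| Assumed q | n = 35 | n = 40 |
|---|---|---|
| 10% | 2% | 1.5% |
| 15% | 14% | 14% |
| 20% | 40% | 41% |
| 25% | 68% | 70% |
| 30% | 87% | 89% |

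**4. Which way q might lie.** Suppose a fraction f of participants want ACP and would complete untreated at rate d, while the rest complete at rate b. Then q = f·d + (1−f)·b. All three inputs are assumptions.

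- f = 0.25, d = 0.30, b = 0.10: q = 0.075 + 0.075 = 15%, rejection 14%.
- f = 0.25, d = 0.30, b = 0.05: q = 0.075 + 0.0375 = 11.3%, rejection 3.7%.
- f = 0.25, d = 0.30, b = 0.02: q = 0.075 + 0.015 = 9%, rejection 1.1%.
- f = 0.50, d = 0.50, b = 0.10: q = 0.25 + 0.05 = 30%, rejection 87%.

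The untreated rate can fall on either side of 10%, depending on inputs the protocol does not contain.

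**5. What an interval would show.** If 12 of 40 complete (30%), the exact (Clopper-Pearson) 95% CI is 16.6% to 46.5%. It excludes 10% and includes 25%. The first fact has no causal meaning here. The second shows how precisely the study can speak to its own progression criterion.

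**The case against.** The strongest reply is that the protocol never commits to this test. Section 5.5.2 names none for the primary endpoint. The 8–10% appears only in section 5.5.1, after the statement that no formal calculation is needed and beside the admission that no data exist, and two values are tried. Read that way, they are already planning values. Objective 4 in section 3 is to estimate completion, the phase III decision in section 6 uses completion above 25% together with acceptability, recruitment and retention, and the efficacy aim in section 1 is described as preliminary. The lack of a control is inherent in a declared single-arm pilot.

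Most of this stands and limits the point. It does not remove it: Table 3 specifies a null, an alternative, alpha and power for a comparison, section 5.5.2 sets a significance threshold, and section 2 states a directional causal hypothesis. Nothing in the protocol says that the 8–10% must not serve as the comparator.

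A reader might also infer that selection biases the comparison in favour of the intervention, so that a false positive is likely. The documents do not support that. Excluding completers and following for only six months pull the untreated rate below a population prevalence, while selection on desire for ACP pulls it up. Section 1 says that ACP uptake is low and professionals hesitant, which makes high untreated uptake doubtful. Desire for ACP is only one of seven alternative qualifying conditions, and its frequency among participants is not given.

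**Conclusion.** The point holds as a mismatch between the reference value and the endpoint, not as a demonstrated bias in a known direction or an error in the sample size. The 8–10% is not the untreated six-month rate of the enrolled patients, and the net direction of the discrepancy cannot be determined. If a test against 10% is run, which is an inference from Table 3 and the 0.05 rule, rejection would not show higher completion because of the intervention: with no effect at all, its probability at n = 35 runs from about 2% to 87% as the assumed untreated rate goes from 10% to 30%, and it falls to about 1% if that rate is 9%. The go decision does not depend on this comparison. What is affected is what the study may claim about its first hypothesis.

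**What to change.** In sections 5.5.1–5.5.2, report the primary endpoint as a proportion with an exact 95% CI, read against the >25% go criterion in section 6. State that 8–10% is a planning value only and that exceeding it is not evidence of an intervention effect. In section 2, align the first hypothesis with objective 4, so that this study estimates completion and the question of an increase is left to the randomised trial.

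Describing completion by qualifying condition is optional. It would be descriptive only, because the conditions overlap and about 40 patients give imprecise rates.

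The changes are to wording and reporting; no extra patients, visits or instruments are needed. The sponsor gives up a p-value-based efficacy statement on the primary endpoint.
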